### Secondary outcomes

Secondary outcomes will be compared between patients receiving the CSP intervention with patients receiving standard care, from baseline to study endpoint.

#### Patient activation

Change in mean PAM-13 score (continuous, 0 to 100) and patient activation levels (categorical, level 1 to 4)

#### Healthcare Services Utilisation and Cost

Change in healthcare utilisation in terms of number of polyclinic, emergency department, hospital admissions and SOC visits from one year preceding recruitment to the period between the first and the second annual reviewChange in healthcare cost in terms of total healthcare cost from polyclinic, emergency department, hospital admissions and SOC visits from one year preceding the first annual review to the period between the first and the second annual review

### Other pre-specified outcomes

Additionally, there are other planned outcomes to be evaluated.

#### Clinical and Biochemical Indicators

Change in mean body weight (kg) of patientsChange in proportion of patients meeting their target blood pressure levelsChange in proportion of patients meeting their target LDL-cholesterol levels

#### Lifestyle Measures

Change in exercise duration (minutes per week) in patientsChange in smoking prevalence and cigarettes smoked daily in patientsChange in proportion of patients with community resource utilisation in the past year

#### Screening Adherence

Change in diabetes retinal photography rates, diabetes foot screening rates in patients

## Sample size calculation

The sample size calculation was based on HbA1c, the primary outcome measure, for which a difference of 0.5 percentage points was taken to be clinically meaningful. The sample size of 1620 was calculated based on 1:1 allocation into the Intervention and Control, 6 pre-specified subgroups (with 3 age tertiles and 2 gender groups), at a power of 90%, with an alpha value of 0.05 (95% confidence interval) and accounting for an attrition rate of 30%. The study team aims to recruit a total of 1620 patients across the four sites.

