### Study setting

PACE-D is conducted in the polyclinics at National University Polyclinics (NUP), the westernmost of three major administrative primary care healthcare groups in Singapore. Each polyclinic is staffed by 15–25 primary care physicians (PCPs) deployed in multi-disciplinary teams which include nurses and clinical pharmacists, with access to the psychologist, dietitian and medical social worker. In addition to the management of acute episodic conditions, the polyclinics provide for the efficient care of the patient with LTCs: laboratory services allow for rapid investigative reporting; surveillance programmes ensure the systematic detection of diabetic retinopathy, neuropathy and nephropathy; and workflows designed to target specific needs through the use of teamlets, [24] tele-consults, [25] and multidisciplinary case discussions [26, 27].

At the polyclinics under NUP, primary care is delivered to patients with LTCs through care teams known as teamlets. Each teamlet provides LTC care to a regular pool of approximately 5000 patients. It is formed by two PCPs and one care manager (CM) who is a chronic disease management-trained senior nurse. These three HCPs are supported by a care coordinator (CC) who schedules consultation and preventive health screening appointments for teamlet-empanelled patients.

In PACE-D, four of the six NUP polyclinics are involved in the study, with two of them designated as Intervention and the other two as Control. In each of these polyclinics, one teamlet is involved in the study and is supported by a PACE-D Coordinator (PC). The role of the PC is to recruit participants and obtain consent for participation, prepare the care planning letter (CPL) for mailing to the participants in the Intervention, and to administer questionnaires to all participants.

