## Statistical methods

### Statistical analyses

Descriptive statistics of the baseline data will be reported, and exploratory data analysis will be conducted prior to model building. Continuous variables will first be tested for normality of distribution. Bivariate analyses will be conducted for continuous variables, and chi-squared test or Fisher’s exact test for categorical variables will be used to determine statistically significant differences between the Intervention and the Control for each baseline characteristic. The analysis will be conducted with the intention-to-treat (ITT) principle unless otherwise specified. Missing endpoints will be imputed with the last observation carried forward (LOCF).

Generalised linear regression will be used to analyse the study endpoint (HbA1c) and while controlling for baseline HbA1c as a covariate. PAM-13 score and other secondary continuous outcomes variables will follow the same analysis methods unless otherwise stated. Logistic regression will be utilised to assess binary outcomes such as screening compliance in the past year, smoking status, and frequent exercise status. Covariates and interaction terms to be included in the model will be selected through inquiry of the data and reviewing existing literature. A stepwise process will be used to drop covariates that have a *p*-value greater than or equal to 0.2. Akaike information criterion (AIC) will be used to decide on the linear model used for potentially non-normal dependent variables such as total cost. Covariates included in the various models will be reported. The outcomes will be compared between the Intervention and the Control. Statistical tests will be conducted at a 2-sided alpha level of 0.05 with confidence intervals calculated at 95%, 2-sided unless otherwise stated. All analysis will be conducted using the STATA software version 16.

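### The stated 90% power for 1620 patients shows no allowance for clustering, although whole polyclinics, two per arm, are allocated

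*Protocol article*

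**What the plan says.** The Sample size calculation section of the protocol article takes HbA1c as the basis, for which "a difference of 0.5 percentage points was taken to be clinically meaningful". On the total and the arms it reads: "The sample size of 1620 was calculated based on 1:1 allocation into the Intervention and Control". The remaining inputs it names are six age-by-sex subgroups, 90% power, an alpha of 0.05 and 30% attrition. It gives no SD, intracluster correlation (ICC), design effect or number of clusters, and it does not say whether the 90% refers to the overall comparison or to each subgroup.

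Under Study setting, the unit allocated is the clinic: "four of the six NUP polyclinics are involved in the study, with two of them designated as Intervention and the other two as Control". The same section adds that a single teamlet takes part at each site, so each arm consists of two clinics and two care teams.

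Under Statistical analyses, HbA1c is analysed by a patient-level regression that adjusts for baseline HbA1c. No clinic or teamlet term is named there.

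**The concern.** Patients in one clinic share the same two physicians, care manager and coordinator, so their HbA1c outcomes are likely to be correlated. A calculation that treats 1620 patients as independent then overstates the information in the trial. Between-clinic variation also does not shrink when more patients are recruited in the same four clinics.

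The 90% is the figure a reader will use to interpret a null result. If it is too high, a non-significant HbA1c result, above all within an age-by-sex subgroup, would be taken as good evidence against a 0.5-point effect when it is weaker than that. The point is separate from how the regression is specified. Adding clinic-robust standard errors to the analysis would leave the power statement as it is, and further from what the analysis delivers.

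**Working it through.** **Inputs from the article.** Total 1620, 1:1; difference 0.5; six subgroups; power 90%; alpha 0.05, two-sided ("Statistical tests will be conducted at a 2-sided alpha level of 0.05", under Statistical analyses); attrition 30%; four clinics, two per arm.

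**Assumed, because not given.** The SD (back-solved below) and the ICC (shown as a range).

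**Step 1: the stated figure.** Completers: 1620 × 0.7 = 1134. Per arm per subgroup: 1134 / 12 = 94.5. The individual-allocation formula is n = 2 × SD² × (1.960 + 1.282)² / 0.5². Solving for the SD at n = 94.5 gives 0.5 × √(94.5 / (2 × 10.507)) = 1.060. With whole-number rounding, an SD of 1.05 gives a total of 1596 and an SD of 1.06 gives 1632. If attrition was applied by multiplying by 1.3, SDs of 1.10 and 1.11 give the same two totals. So 1620 can be matched, not strictly reproduced.

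**Step 2: is the match proof?** No. The same formula with six subgroups, an SD of 0.75 and a design effect of 2 gives 2 × 0.75² × 10.507 / 0.25 = 47.28 per arm, and 47.28 × 12 × 2 / 0.7 = 1621. One overall comparison with an SD of 1.5 and a design effect of 3 gives 189.1 × 2 × 3 / 0.7 = 1621.

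**Step 3: power with clustering, SD 1.06, no baseline adjustment.** Completers per clinic: m = 94.5 / 2 = 47.25 in a subgroup and 1134 / 4 = 283.5 overall. Design effect DE = 1 + (m − 1) × ICC. With two clinics per arm, the standard error of the arm difference is SE = SD × √(DE / m). Power follows from 0.5 / SE, either with a normal critical value or from the noncentral t on 2 degrees of freedom (four clinics minus two arms).

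| ICC (assumed) | Subgroup DE | Subgroup SE | Subgroup power, normal | Overall DE | Overall SE | Overall power, normal | Overall power, 2 df |
|---|---|---|---|---|---|---|---|
| 0.005 | 1.23 | 0.171 | 83% | 2.41 | 0.098 | 99.9% | 73% |
| 0.01 | 1.46 | 0.186 | 76% | 3.83 | 0.123 | 98% | 57% |
| 0.02 | 1.93 | 0.214 | 65% | 6.65 | 0.162 | 87% | 40% |
| 0.05 | 3.31 | 0.281 | 43% | 15.1 | 0.245 | 53% | 22% |

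Overall power falls below 90% above an ICC of about 0.018 with a normal critical value, and above about 0.0013 on 2 df.

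**Step 4: unlimited patients in the same four clinics.** SE tends to SD × √ICC. At ICC 0.01 that is 0.106, so 0.5 / 0.106 = 4.72, and power on 2 df is at most about 68%.

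**Step 5: baseline adjustment.** If 1.06 is a raw SD and the baseline-endpoint correlation is 0.6 (an assumption), the residual SD is 1.06 × √(1 − 0.36) = 0.848. Holding the ICC at 0.01, the subgroup SE is 0.848 × √(1.46 / 47.25) = 0.149 and power is 92% with a normal critical value. Overall, SE is 0.848 × √(3.83 / 283.5) = 0.0986, and power is 99.9% with a normal critical value and 73% on 2 df. The ceiling of step 4 becomes 0.5 / 0.0848 = 5.90, or about 83%.

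**The case against.** Four objections have weight.

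- **The input list is incomplete.** No sample size for a difference in means can be computed without an SD, and none is printed. A design effect could therefore also have been left out when the full protocol was condensed. A reader might infer from the match at SD 1.06 that no design effect can be hidden in 1620. Step 2 shows that this inference fails. What remains is that the article attaches 90% to a list of inputs, down to subgroups and attrition, in which nothing allows for clinics.
- **The 2 df figures assume a test the article does not plan.** This is correct. On 2 df, subgroup power would be only 43% even at an ICC of zero, so that loss comes from the reference distribution and not from clustering; it is not used here. For the overall comparison both versions are shown, because the article names no analysis that allows for clinics and a normal critical value is hard to defend with two clinics per arm.
- **The overall comparison has slack.** If 1620 arose by multiplying by six, overall power is 98% at ICC 0.01 with a normal critical value. A reader might infer that the primary comparison is plainly underpowered. The documents do not support that: it depends on an ICC they do not give and on the test chosen.
- **Baseline adjustment is planned.** It could restore about 92% per subgroup at ICC 0.01. It also means that the relevant quantities are the residual SD and the ICC of baseline-adjusted HbA1c, not the raw ones. It does not bring the overall figure on 2 df back to 90% in that example.

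**Conclusion.** The point holds as a defect in the stated power. As printed, the 90% shows no allowance for the allocation of four whole polyclinics. If 1620 was sized per subgroup at an SD near 1.06 without baseline adjustment, any positive ICC takes subgroup power below 90%: from 83% at ICC 0.005 to 43% at 0.05, with a normal critical value. Overall, the conclusion turns on the test: 90% survives up to an ICC of about 0.018 with a normal critical value, but only to about 0.0013 on 2 df.

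These sizes rest on a back-solved SD, assumed ICCs and equal numbers per clinic and subgroup, so no single corrected power can be given. It is not established that a design effect was omitted from the underlying calculation, nor that the overall primary comparison falls short of 90%.

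**What to change.** Keep 1620. In the Sample size calculation section:

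1. State the SD and whether it is raw or baseline-adjusted.
2. Say whether the 90% applies to the overall comparison or to each subgroup.
3. Say that it holds only if outcomes are independent within clinics, or give the design effect if one was used.
4. Estimate the clinic ICC of baseline-adjusted HbA1c from the polyclinics' routine records. The healthcare group has only six polyclinics, so the estimate will be imprecise and a range should be carried forward.
5. Restate the power, or the detectable difference, overall and per subgroup, using 1 + (m − 1) × ICC and the degrees of freedom that four clinics allow.

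The cost is a few lines of text and one query of routine records, with no extra patients. The downside is a less favourable stated power. Recruiting more patients in the same clinics is not a substitute, because the between-clinic component stays.

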### Study population

The study population comprises patients currently receiving care from a designated teamlet in each of the four NUP polyclinics. Patients are recruited if they meet all of the following inclusion criteria: (1) adults with diabetes mellitus aged 21 years old and above; the (2) ability to provide informed consent; (3) ability to communicate in English, Malay or Chinese and (4) ability to comprehend the CPL on their own or with the assistance of family members.

Patients are not eligible for the study if they are (1) pregnant, or unable to engage with the CPL and/or CSP conversation because of any of the following: (2) cognitive impairment; (3) psychotic disorders; and (4) severe hearing/visual impairment.

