### Subgroup analyses

HbA1c levels are known to be related to gender and age amongst patients with diabetes in various population groups, which may be attributed to a multitude of factors such as biological differences and disease progression status. However, the relationship between gender and patient activation has yielded inconsistent results in various different population context [30, 31]. To elucidate these relationships under the unique context, pre-specified subgroup analysis will be conducted to evaluate HbA1c. The model for subgroup analysis would include treatment group, time, with sex and age category (3 strata, “18–49”, “50–64” & “65 and above”) as fixed effects, adjusting for covariates identified in model building. The significance will be adjusted using false discovery rate correction to account for multiple testing [32].

Exploratory analysis will also be conducted for the variables HbA1c and PAM-13 score to examine the effects of the programme across different population subgroups. The following subgroups will be assessed: ethnicity, years since diagnosis of diabetes at baseline, HbA1c at baseline, education, and baseline insulin use. The purpose of the analyses is for exploratory purposes and to guide hypothesis generation and inform subsequent research studies [33].

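### The 90% subgroup power was set for age tertiles at an unadjusted 0.05 and does not carry over to the planned analysis by fixed age bands with a false discovery rate correction

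*Protocol article*

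**What the plan says.** Under Sample size calculation, the target rests on an HbA1c effect for which "a difference of 0.5 percentage points was taken to be clinically meaningful", on equal allocation, on 30% attrition, and on "6 pre-specified subgroups (with 3 age tertiles and 2 gender groups), at a power of 90%, with an alpha value of 0.05". The total of 1620 is then the recruitment aim: "The study team aims to recruit a total of 1620 patients across the four sites". That section mentions no multiplicity adjustment.

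Under Subgroup analyses, the pre-specified HbA1c analysis has a model with treatment group, time, and "sex and age category (3 strata, “18–49”, “50–64” & “65 and above”) as fixed effects", plus covariates. It then adds: "The significance will be adjusted using false discovery rate correction to account for multiple testing".

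Under Study population, entry is limited to "adults with diabetes mellitus aged 21 years old and above".

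The article gives no SD for HbA1c, no expected age or sex distribution, and no name for the false discovery rate procedure.

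**The concern.** The two sections disagree on two inputs that determine subgroup power.

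- **How the age strata are formed.** Tertiles put one third of patients in each age group. Fixed cut points put in each group whatever share the clinic population supplies.
- **The significance level.** The sizing uses 0.05 for each comparison. The analysis applies a correction whose threshold can never be more lenient than 0.05.

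A smaller mismatch is that the lowest band starts at 18 although nobody under 21 can enrol. That is a labelling slip and changes no result.

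This matters because the six subgroups appear to account for most of the recruitment target. If their power is overstated, a non-significant result in a thin band could be taken for a well-powered negative. Having two definitions of the age strata on record also leaves open which one will be reported.

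**Working it through.** **Inputs from the article.** Difference 0.5 points; power 90%; two-sided 0.05 (Statistical analyses); 1:1 allocation; six subgroups; attrition 30%; total 1620.

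**Inputs not in the article, so assumed.** The SD (solved for below), equal sexes within each age group, the share of patients in each band, and Benjamini-Hochberg over six tests as the false discovery rate procedure.

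**1. Fitting the stated total.** 1620 / (6 × 2) = 135 per arm per cell; after attrition, 135 × 0.70 = 94.5. Setting n = 2 × SD² × (1.960 + 1.282)² / 0.5² equal to 94.5 gives

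SD = (0.5 / 3.242) × √(94.5 / 2) ≈ 1.06.

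In the other direction, SD 1.055 gives 94 per arm, 94 / 0.70 rounded up to 135, and 135 × 12 = 1620 exactly. Under the same formula but without the six cells, SD 1.055 needs only 2 × 94 / 0.70 ≈ 269 patients in all, and reaching 1620 would need an SD of about 2.60. Six equal cells, each at 90% and unadjusted 0.05, is therefore the natural reading. Because the SD is solved for, this is a consistency check and not an independent reproduction.

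**2. Effect of unequal bands.** There are 1620 × 0.70 = 1134 completers. A band with share f, split equally by sex and arm, has n = 1134 × f / 4 per arm per cell. Power = Φ(0.5 / (1.06 × √(2/n)) − 1.96), using the unrounded SD of 1.0603:

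| Assumed share of band | n per arm per cell | Power per cell, unadjusted 0.05 |
|---|---|---|
| 33.3% | 94.5 | 90% |
| 30% | 85.0 | 87% |
| 25% | 70.9 | 80% |
| 20% | 56.7 | 71% |
| 15% | 42.5 | 58% |
| 10% | 28.4 | 43% |

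For the 20% row: 0.5 / (1.0603 × √(2/56.7)) = 2.51; 2.51 − 1.96 = 0.55; Φ(0.55) ≈ 0.71.

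The six cell shares sum to one. Unless all six are equal, at least one is below one sixth and so below 90%.

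**3. Effect of the correction, with equal cells.** If only one cell has an effect, the first Benjamini-Hochberg step is 0.05 / 6 = 0.0083, with critical value 2.638. Power is then about Φ(3.242 − 2.638) = Φ(0.60) ≈ 0.73. A simulation of the full procedure (200,000 runs) gives 0.735 for that case and 0.892 when the effect is in all six cells. The loss is therefore about 1 point in one case and 16 to 17 points in the other.

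**4. Both together.** With bands of 20%, 40% and 40%, power in a cell of the 20% band is about 69% if all six cells have the effect and about 46% if only that one does.

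**5. Primary comparison.** With 567 completers per arm and the same SD, power exceeds 99%, ignoring clustering by clinic.

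**The case against.** A reader might go further and infer that the cells under 50 will lack power. The documents do not support that. It needs fewer than one third of patients to be under 50, and no age distribution is given. The table shows what a share would imply, not what the share will be.

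A reader might also infer that tertiles would secure the 90%. They equalise only the age margin. They do not equalise sex within age, nor the arms within a cell when allocation is by clinic. With exact tertiles and a 40/60 sex split, the smaller cells have n = 94.5 × 0.8 = 75.6 per arm and about 83% power. Reverting to tertiles is therefore not a full remedy, and it would replace fixed cut points with data-derived ones.

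Nor does the article say outright that each subgroup has 90% power. It lists the six subgroups among the inputs, and the per-cell reading is inferred from a back-solved SD.

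The per-cell figures may also not match the eventual tests:

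- The subgroup section lists fixed effects and does not spell out six separate contrasts. If a 20% band were tested with the sexes combined, n = 113.4 per arm and power is about 94% at 0.05.
- The main model adjusts for baseline HbA1c. If 1.06 is an unadjusted SD and the baseline-endpoint correlation is assumed to be 0.5, 71% becomes 83% and 80% becomes 90%.
- Missing endpoints are carried forward, so more than 1134 patients may be analysed. The sizing, however, itself discounts for 30% attrition.

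These objections stand as limits on the size of the shortfall. They do not remove the mismatch: strata and significance level differ between the two sections, and an analysis that does not test six cells would be a further departure from a sizing built on six subgroups.

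**Conclusion.** The point holds as an inconsistency between two current sections. No arithmetic error in 1620 is shown. The sizing uses tertiles at an unadjusted 0.05, the analysis uses fixed bands under a false discovery rate correction, and the 90% does not transfer from one to the other.

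The size depends on facts the article does not give. On six cells with SD about 1.06, 30% attrition and equal sexes, an assumed 20% band gives about 71% per cell. Under Benjamini-Hochberg with equal cells, the loss from the correction runs from about 1 point to about 17, depending on how many cells carry the effect. Which band is thin cannot be told from the article.

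The primary overall comparison is untouched by this point, so the matter should be corrected but does not threaten the main result.

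**What to change.** 1. Use one definition of the age strata in both sections. Keeping the pre-specified fixed bands is the simpler choice, with the first labelled 21–49 to match the entry age.
2. In the sample size section, state the SD used and the expected age-by-sex distribution, for example from the teamlets' patient registers.
3. Name the false discovery rate procedure and the set of tests it covers, and restate subgroup power for the chosen strata at the adjusted level. Alternatively, state that 90% power is not claimed for each subgroup.

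The cost is a recalculation, some wording and a less favourable stated subgroup power. No extra patients are needed.

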## Statistical methods

### Statistical analyses

Descriptive statistics of the baseline data will be reported, and exploratory data analysis will be conducted prior to model building. Continuous variables will first be tested for normality of distribution. Bivariate analyses will be conducted for continuous variables, and chi-squared test or Fisher’s exact test for categorical variables will be used to determine statistically significant differences between the Intervention and the Control for each baseline characteristic. The analysis will be conducted with the intention-to-treat (ITT) principle unless otherwise specified. Missing endpoints will be imputed with the last observation carried forward (LOCF).

Generalised linear regression will be used to analyse the study endpoint (HbA1c) and while controlling for baseline HbA1c as a covariate. PAM-13 score and other secondary continuous outcomes variables will follow the same analysis methods unless otherwise stated. Logistic regression will be utilised to assess binary outcomes such as screening compliance in the past year, smoking status, and frequent exercise status. Covariates and interaction terms to be included in the model will be selected through inquiry of the data and reviewing existing literature. A stepwise process will be used to drop covariates that have a *p*-value greater than or equal to 0.2. Akaike information criterion (AIC) will be used to decide on the linear model used for potentially non-normal dependent variables such as total cost. Covariates included in the various models will be reported. The outcomes will be compared between the Intervention and the Control. Statistical tests will be conducted at a 2-sided alpha level of 0.05 with confidence intervals calculated at 95%, 2-sided unless otherwise stated. All analysis will be conducted using the STATA software version 16.

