### Clinical data collection and follow-up assessments

Clinical outcomes data used for assessment is collected as part of routine practice for diabetes management in NUP, based on local clinical practice guidelines, and will be extracted from the EMR for purposes of this study. The clinical measurements are as listed in Table 1.

Survey questionnaires administered following each of the scheduled annual reviews include PAM-13, engagement in self-care activities, diabetes medication status (binary question on oral anti-diabetic medication and insulin therapy), and foot and eye screening attendance. Patients in the Intervention will receive an additional survey to rate their perception of the new care model. Results of routine blood tests, clinical markers and survey questionnaires administered throughout the study will be stored into REDCap, a secure browser-based platform for capturing of consent forms and research data electronically.

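### Last observation carried forward is the only stated method for missing HbA1c endpoints, and the schedule makes the carried value the pre-intervention baseline unless a routine interim test exists

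*Protocol article*

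**What the plan says.** The Statistical analyses section sets two rules that work together. First, "The analysis will be conducted with the intention-to-treat (ITT) principle unless otherwise specified", so patients who drop out stay in the comparison. Second, "Missing endpoints will be imputed with the last observation carried forward (LOCF"). No alternative method and no sensitivity analysis is given. The primary model regresses endpoint HbA1c on study group with baseline HbA1c as a covariate.

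The Sample size calculation section states that "a difference of 0.5 percentage points was taken to be clinically meaningful" and sets the total at 1620, "accounting for an attrition rate of 30"%.

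The Primary outcome section takes as baseline the last HbA1c before the first annual review, and as endpoint the HbA1c at the second. Table 1 places HbA1c only in the blood panel before each of these reviews. Any reading in between comes from routine care: the section on the current care model describes interim reviews at which laboratory tests are done if indicated. The article also says "Clinical outcomes data used for assessment is collected as part of routine practice for diabetes management in NUP", and that these data are extracted from the electronic medical record (EMR).

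**The concern.** LOCF assumes that HbA1c would have stayed at its last recorded value. Here the study itself schedules no HbA1c between baseline and endpoint, so for a patient with no routine interim test the method becomes baseline carried forward and the imputed change is exactly zero. Where an interim value does exist, it exists because someone judged a test to be indicated, so the time point carried forward varies with how well the diabetes is controlled.

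Two consequences follow for the primary estimate. A real effect is pulled towards zero in proportion to the share of Intervention endpoints filled this way. If the arms lose patients at different rates while HbA1c drifts in both, the arm that loses more is credited with less of the drift, and a difference appears where none exists. Allocation is open, non-randomised and by clinic, so unequal loss is plausible, although the article does not predict it.

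**Working it through.** **Inputs from the article.** Total 1620, 1:1 (810 per arm); attrition 30%; target difference 0.5; "at a power of 90%, with an alpha value of 0.05 (95% confidence interval"); two-sided testing ("Statistical tests will be conducted at a 2-sided alpha level of 0.05"); and "1:1 allocation into the Intervention and Control, 6 pre-specified subgroups (with 3 age tertiles and 2 gender groups").

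**Assumptions, not in the article.** SD of HbA1c, baseline-endpoint correlation, drift, dropout split, random dropout, no interim readings, arms alike at baseline.

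**Plan's own figure.** No SD is given, so 1620 cannot be reproduced directly. Solving backwards over 2 arms × 6 subgroups: 1620 × 0.7 / 12 = 94.5 evaluable per arm per subgroup. SD = 0.5 × √(94.5/2) / (1.960 + 1.282) = 1.06. This was used as one assumed SD (correlation 0.60), with SD 1.3 and correlation 0.65 as a second.

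**Endpoints at risk.** At most 0.30 × 1620 = 486.

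**Expected LOCF estimate.** Let τ be the true reduction, δ the common drift, and d_I and d_C the missing proportions. With baseline carried forward, the Intervention minus Control difference is

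(1 − d_I)(δ − τ) − (1 − d_C)δ = −τ(1 − d_I) + δ(d_C − d_I).

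The formula does not involve the SD or the correlation.

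*True effect 0.50, no drift:*
- 30% missing in both arms: 0.50 × 0.70 = 0.35.
- 15% in both arms: 0.50 × 0.85 = 0.425, about 0.43.
- 20% Intervention, 40% Control: 0.50 × 0.80 = 0.40.
- 40% Intervention, 20% Control: 0.50 × 0.60 = 0.30.

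*No true effect, drift +0.3:*
- 30% in both arms: 0.
- 35% Intervention, 25% Control: 0.3 × (−0.10) = −0.03.
- 40% Intervention, 20% Control: 0.3 × (−0.20) = −0.06.
- Drift −0.3 with 40% and 20%: +0.06.

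**Simulation check** (baseline-adjusted regression, 810 per arm). With 30% missing in both arms and a true 0.50, LOCF averages 0.35 and the observed endpoints average 0.50. With no effect, the rejection rates at nominal 5% are:

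| Dropout gap, drift 0.3 | SD 1.06, r 0.60 | SD 1.3, r 0.65 |
|---|---|---|
| none | about 5% | about 5% |
| 10 points | about 13–14% | about 10–12% |
| 20 points | about 34–37% | about 29–30% |

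These ignore clustering by clinic.

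**Standard errors at 30% missing.** For observed endpoints (567 per arm) the SE is SD × √(1 − r²) × √(2/567): 1.06 × 0.80 × 0.0594 = 0.050, and 1.3 × 0.760 × 0.0594 = 0.059. The LOCF model SE is 0.037 and 0.043. In the simulations it agrees with the actual spread of the LOCF estimates (0.037 and 0.043).

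**The case against.** The strongest reply concerns size, and much of it stands.

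- **Fewer endpoints may be missing.** The 30% is a planning rate for attrition, not a forecast of absent HbA1c. Outcomes come from the routine record, so a patient who stops the surveys may still have an annual-panel result. A reader might infer that 486 endpoints will be filled in; the article supports that only as a ceiling.
- **Baseline is not always the carried value.** Interim reviews occur in routine care, and the LOCF rule is not limited to scheduled readings. The share of patients with such a reading is unknown, and the calculation sets it to zero.
- **The benchmark of 0.50 assumes dropouts would have had the full effect.** Enrolment comes about three months before the first annual review, so some may leave before any care and support planning conversation.
- **Dilution is conservative for a superiority claim.** In the SD 1.3 case 0.35 / 0.043 is about 8 standard errors before clustering, so the overall test would still reject. What is damaged is the estimate, read against a threshold of 0.5.
- **False positives need assumed drift and unequal loss.** Both arms receive the same voucher. If clustering were reflected in the SE (assumed intraclass correlation 0.005 to 0.01, 405 per clinic, design effect 3.0 to 5.0), a normal approximation at SD 1.3 gives rejection of roughly 6–7% for the 10-point gap and 10–13% for the 20-point gap.

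Two stronger readings fail. One is that the LOCF standard error is miscalculated because copied values count as measured. It is smaller than the observed-data SE, but it matches the actual spread of the LOCF estimator; the fault is that this estimator is centred on the wrong value. The other is that inflating the sample for attrition contradicts keeping dropouts in the analysis. Doing both is common under ITT and is not an inconsistency in the article.

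None of this makes LOCF a sound primary method. Nor can it be left to an unseen analysis plan, because the article states the rule outright.

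**Conclusion.** The point holds. LOCF is fixed as the sole method for missing endpoints in a design whose only scheduled earlier HbA1c precedes the intervention. The dilution is arithmetic once baseline is carried: 0.50 becomes about 0.35 at 30% missing in both arms and about 0.43 at 15%. The first figure is an upper bound at equal dropout, because routine results and interim tests would reduce it.

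With no true effect and equal dropout there is no bias. A spurious difference of 0.03 to 0.06, of either sign, requires both a common drift (0.3 assumed) and a dropout gap of 10 to 20 points (assumed). Type I error is then about 10 to 30% at SD 1.3, somewhat higher at SD 1.06, and lower once clustering is accounted for. These are illustrations; the article does not support reading them as a prediction that the trial will produce a false effect. The main fault is bias in the primary estimate, which the method builds in and which can be avoided at little cost.

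**What to change.** In Statistical analyses, replace LOCF as the primary method with one that is valid under missing at random. Either of these would do:

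1. Multiple imputation by arm, with baseline HbA1c, any interim HbA1c from the EMR, the adjustment covariates and clinic in the imputation model.
2. A likelihood-based mixed model on all available HbA1c values.

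Keep LOCF only as a sensitivity analysis.

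Leave the endpoint in the Primary outcome section as it is. Only for patients with no HbA1c at the second annual review, use a routine EMR HbA1c within a window fixed in advance, where consent allows. This should not redefine the endpoint for everyone else.

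The cost is a revised analysis paragraph, a limited extra EMR query with a check of what the consent covers after a patient leaves the study, a little more analysis work, and a somewhat larger standard error than LOCF would show. No visit, test or recruitment target changes.
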